### Trial procedures

The time schedule of enrolment, interventions, assessments is shown in Fig. 1.

**Fig. 1 Fig1:**
[figure not shown]
Study timeline detailing enrolment, interventions and assessments

#### Randomisation

Simple randomisation will be used to allocate schools to either of the two interventions within each stratum. A third-party (statistician) will generate the allocation sequence using computer-generated random numbers and will inform the principal investigator (not directly involved in data collection), who will subsequently send separate fieldwork teams to schools.

#### Blinding

Participants cannot be blinded in this study given the nature of the interventions. Children and their parents will know they are taking part in a trial (after reading the information sheet) and whether their children will be allocated to the intervention or comparison group from the referral letter. Outcome assessors will be blinded by sending separate fieldwork teams (who will not be aware of the study aims) for the intervention and comparison groups. We have also chosen untreated dental caries as our primary outcome (rather than self-reported dental visits) as the former is considered more reliable and less prone to measurement bias. Self-reported dental visits could be influenced by participants’ and their parents’ knowledge of which trial group they are in.

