### Data collection

The study will obtain approval from the Saudi Ministry of Health to ensure no screening programme is implemented in the selected schools and from the Ministry of Education to both obtain the list of schools in Riyadh city and access to the selected schools. Approval will also be obtained from KSU-DC to refer children to the dental clinic.

After obtaining these approvals, the primary researcher will send invitation letters to selected schools. Refusals and non-respondent schools will be replaced with new schools randomly chosen from the same list. For schools that agree to participate, the primary researcher will organise dates and times for data collection in meetings with heads of schools.

In the schools that agree to participate, the participants’ information sheet, a written informed consent form and a structured questionnaire will be sent to parents in the children’s school bag. A text message from the school administration will be sent on the same day informing parents about the documents and encouraging participation. A new text message will be sent after 1 week to all parents thanking those who have already agreed to participate and reminding parents who have not sent the forms back to do so before the fieldwork team visits the school. The parental questionnaire has been modified from the WHO questionnaire for assessing oral health status [20] to collect data on sociodemographic characteristics (children’s age and gender, household size, parental education and family income), dental visits, oral hygiene behaviour and diet of the child. Parents will return the signed consent forms and completed questionnaires with their children. A shorter version of the questionnaire (focussing on the child’s last dental visit during the last 12 months) will be sent to all parents a week prior to the second visit to schools for the follow-up clinical examinations.

Only children with signed parental consent will be clinically examined. The fieldwork team will explain the activities to be carried out in the classroom. Signed consent forms and parental questionnaires will be collected at this stage and children’s eligibility checked. Before examining every child, the recorder will ask children whether they had visited the dentist in the last 12 months, and if so, the reason for that visit will be recorded. The same question will be asked to children during follow-up clinical assessments (‘since we last saw you’).

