There will be 12 dentists doing the fieldwork under the supervision of the principal investigator. Each fieldwork team will consist of an examiner who will perform clinical examinations and a recorder who will register codes in examination forms. Individuals will switch roles to minimise visual fatigue. They have been trained and calibrated before the beginning of the trial. Mean Kappa values for inter- and intra-examiner reliability in caries diagnosis at tooth level were 0.78 and 0.86, respectively. The principal investigator will hand over referral letters to screened-positive children in girls-only schools (instructing them to put them in the school bags and taking them to their parents). A male organiser, who will not be involved in dental examinations, will do the same in boys-only schools.

Clinical examinations for dental caries will be performed according to WHO criteria that defines dental caries at the caries into dentine threshold [20]. No radiographs will be taken. Examinations will be conducted similarly at baseline and follow-up, with children sitting on a school chair, using headlamps, plane mouth mirrors and a periodontal probe. Teeth will not be brushed or professionally cleaned before examination but cotton wool rolls/buds and the periodontal probe will be used, respectively, to dry the surfaces and remove moisture/debris to facilitate visual inspection. Standard infection control measures will be in place.

After clinical examinations at baseline and follow-up, 10% of participants will be re-examined by the same fieldwork team to assess intra-examiner reliability. After clinical examinations in the follow-up assessment (at 12 months) screened-positive children in both trial groups will be referred to KSU-DC (close-out procedure).

Given the training and calibration of examiners in caries assessment, the probability of having false-positive cases is minimal. Upon referral, a standard dental check-up is always conducted as part of the treatment plan where any false-positive cases will be identified. If that occurs, the dentist will inform parents that upon further examination no treatment is required.

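### Each trial group has its own examining teams, so a between-team difference in measured 12-month change in caries cannot be separated from the intervention effect

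*Protocol article*

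**What the plan says.** The Blinding section states that assessors are "blinded by sending separate fieldwork teams (who will not be aware of the study aims) for the intervention and comparison groups". The Randomisation section agrees: the statistician gives the allocation to the principal investigator, "who will subsequently send separate fieldwork teams to schools". Nowhere is a team said to work in both groups.

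On staffing, the Data collection section says: "There will be 12 dentists doing the fieldwork under the supervision of the principal investigator". Each team is one examiner and one recorder, who exchange roles. The Discussion adds that boys' and girls' schools have separate teams.

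On agreement between examiners: "Mean Kappa values for inter- and intra-examiner reliability in caries diagnosis at tooth level were 0.78 and 0.86, respectively". During the trial, "10% of participants will be re-examined by the same fieldwork team to assess intra-examiner reliability".

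Referral letters are given out by the principal investigator in girls' schools. For boys' schools: "A male organiser, who will not be involved in dental examinations, will do the same in boys-only schools".

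The primary outcome is the change over 12 months in the number of teeth with untreated caries, as scored by these teams. The Between-group comparisons section lists stratification, school clustering and baseline socioeconomic and behavioural differences as the factors the model accounts for. Examiner or team is not among them.

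**The concern.** The article chooses a clinical primary outcome partly because it can be assessed blind. The method of blinding then ties the assessors to the groups. If the intervention group's teams come to score dentine caries more or less readily than the comparison group's teams over the year, the estimated effect carries that difference. Team is nested in group, so a fixed team effect and the treatment effect cannot both be estimated.

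Separate teams are not needed to keep assessors blind. Letters go out after the examination and are not tied to the examiners: the principal investigator hands them over in girls' schools and a non-examining organiser does so in boys' schools. A team unaware of allocation could examine schools in either group.

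The same teams also decide who is screened positive, which fixes who is referred and defines one of the supplemental subgroups.

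A smaller, related point is the order of questions. "Before examining every child, the recorder will ask children whether they had visited the dentist in the last 12 months", and the same question is put at follow-up. If that order is kept, the team hears whether the child attended before the teeth are scored.

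**Working it through.** **1. Is team nested in group?** Yes. Blinding and Randomisation both say so, and no other section crosses teams over groups.

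**2. Which team differences survive a change score?** Let a team add a constant *a* to every count.
- Same team at both visits: measured change = (follow-up + *a*) − (baseline + *a*), so *a* cancels.
- Different team at follow-up: the difference between the two teams' constants remains.
- Drift: the part of *a* that changes between visits remains.
- Proportional detection: with assumed true means falling from 4 to 3 in both groups, complete detection gives a change of 3 − 4 = −1.0. Detection of 80% gives 0.8 × 3 − 0.8 × 4 = −0.8. The false difference is 0.2 teeth, and 0.2/0.50 = 40% of the target difference. If the true mean stayed at 4, the false difference would be 0.

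The article says examinations are done similarly at both times. It does not say that the same team returns.

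**3. Would the in-trial check reveal it?** No. The 10% re-examination is by the same team, so it measures consistency within a team and not a difference between the groups' teams.

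**4. Illustration of size.** Stated inputs are a target of 0.50 teeth, 455 evaluable children per group, 80% power, 5% significance (taken as two-sided), ICC 0.03, 75 per cluster, 16 schools and 12 dentists. The outcome SD is not stated, so the figure of 910 cannot be reproduced independently. Working backwards:
- At 75 per cluster, design effect = 1 + 74 × 0.03 = 3.22. Effective n per group = 455/3.22 = 141.3. SD = 0.50 × √(141.3/2)/(1.96 + 0.84) ≈ 1.50.
- At 910/16 ≈ 57 per school, design effect ≈ 2.68 and SD ≈ 1.65.

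Assumptions for the simulation:
- 8 v 8 schools of 56 children, and no true effect.
- 12 dentists in pairs = 6 teams, 3 per group.
- A team effect on measured change with SD τ.
- A two-sample t test on school means. At SD 1.5, the variance of a school mean without team effects is 1.5² × 0.03 + 1.5² × 0.97/56 = 0.0675 + 0.0390 = 0.1065.

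With equal numbers of schools per team, the false group difference has SD τ√(2/3).

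| τ (teeth, in measured change) | SD of false difference | Type I error, SD 1.5 | Type I error, SD 1.65 | Teams spread alike over both groups, SD 1.5 |
|---|---|---|---|---|
| 0.1 | 0.08 | about 7% | 6 to 7% | about 4% |
| 0.2 | 0.16 | about 11% | about 10% | about 3% |
| 0.3 | 0.24 | about 16% | about 15% | about 1.5% |

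The last column falls below 5% because team differences cancel from the contrast but, with no team term in the test, still widen the standard error.

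**The case against.** The strongest reply is that the outcome is a change. If each team returns to its own schools and its threshold is stable, an additive difference does no harm and type I error stays at 5%. That stands, and it limits the point to differences in measured change. A reader might infer that any difference in scoring level passes whole into the treatment effect. The document does not support that for an additive difference with the same team returning.

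Second, examiners were trained and calibrated, and an inter-examiner kappa of 0.78 is real mitigation. A reader might take its being lower than 0.86 as evidence that the groups' teams differ. It is not: inter-examiner agreement is expected to be lower than intra-examiner agreement even when disagreements have no direction. Equally, it does not show that the two sets of teams share a threshold, or that they would still do so 12 months later.

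Third, with several teams per group, part of the team variation enters the between-school variance, so the standard error does reflect some of it. Inference can also allow for it: in the set-up above, a t test on 3 v 3 team means keeps type I error at about 5%. The price is power, since degrees of freedom fall from 8 + 8 − 2 = 14 to 3 + 3 − 2 = 4. The bias actually realised is still not removed. Much larger error rates would follow from one team per group, but 12 dentists working in pairs, with separate boys' and girls' teams, give no ground for that case.

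Fourth, hearing about a dental visit does not identify the group, because screened-positive children in both groups are referred and restorations are visible in any case. This is fair, and it keeps the question order a minor matter.

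**Conclusion.** The confounding is certain: it is written into the design, no section offsets it, and no analysis can separate a fixed team difference in measured change from the intervention effect. Its size is unknown. No between-team SD can be derived from the document, and the error rates of about 7%, 11% and 16% are an illustration. They rest on a back-calculated SD, an assumed equal split into three teams per group, and τ read as a team difference in change, not in scoring level. The matter needs correction because it affects the primary outcome and existing staff can avoid it.

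**What to change.** Replace the Blinding sentence with wording such as: *Every fieldwork team examines schools in both trial groups, balanced within area and school sex (female teams across girls' schools in both groups, male teams across boys' schools in both groups). Teams are not told a school's allocation. The same team examines a school at baseline and at follow-up, and team is a factor in the model.* Bring the Randomisation sentence on sending teams into line.

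The Trial status section shows recruitment from 20 November 2017, with this version dated 13 March 2018, so some schools may already have been examined. For those, crossing teams at follow-up would break the same-team rule. Keep the same team, and report a sensitivity analysis that allows for team-level variation, accepting its lower power.

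At follow-up, put the dental-visit question to the child after the caries examination.

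The cost is rescheduling and protocol wording, with no extra staff. The downside is a small risk that a team working in both groups hears remarks that reveal a school's group. Asking the visit question last reduces it.

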### Data collection

The study will obtain approval from the Saudi Ministry of Health to ensure no screening programme is implemented in the selected schools and from the Ministry of Education to both obtain the list of schools in Riyadh city and access to the selected schools. Approval will also be obtained from KSU-DC to refer children to the dental clinic.

After obtaining these approvals, the primary researcher will send invitation letters to selected schools. Refusals and non-respondent schools will be replaced with new schools randomly chosen from the same list. For schools that agree to participate, the primary researcher will organise dates and times for data collection in meetings with heads of schools.

In the schools that agree to participate, the participants’ information sheet, a written informed consent form and a structured questionnaire will be sent to parents in the children’s school bag. A text message from the school administration will be sent on the same day informing parents about the documents and encouraging participation. A new text message will be sent after 1 week to all parents thanking those who have already agreed to participate and reminding parents who have not sent the forms back to do so before the fieldwork team visits the school. The parental questionnaire has been modified from the WHO questionnaire for assessing oral health status [20] to collect data on sociodemographic characteristics (children’s age and gender, household size, parental education and family income), dental visits, oral hygiene behaviour and diet of the child. Parents will return the signed consent forms and completed questionnaires with their children. A shorter version of the questionnaire (focussing on the child’s last dental visit during the last 12 months) will be sent to all parents a week prior to the second visit to schools for the follow-up clinical examinations.

Only children with signed parental consent will be clinically examined. The fieldwork team will explain the activities to be carried out in the classroom. Signed consent forms and parental questionnaires will be collected at this stage and children’s eligibility checked. Before examining every child, the recorder will ask children whether they had visited the dentist in the last 12 months, and if so, the reason for that visit will be recorded. The same question will be asked to children during follow-up clinical assessments (‘since we last saw you’).

There will be 12 dentists doing the fieldwork under the supervision of the principal investigator. Each fieldwork team will consist of an examiner who will perform clinical examinations and a recorder who will register codes in examination forms. Individuals will switch roles to minimise visual fatigue. They have been trained and calibrated before the beginning of the trial. Mean Kappa values for inter- and intra-examiner reliability in caries diagnosis at tooth level were 0.78 and 0.86, respectively. The principal investigator will hand over referral letters to screened-positive children in girls-only schools (instructing them to put them in the school bags and taking them to their parents). A male organiser, who will not be involved in dental examinations, will do the same in boys-only schools.

Clinical examinations for dental caries will be performed according to WHO criteria that defines dental caries at the caries into dentine threshold [20]. No radiographs will be taken. Examinations will be conducted similarly at baseline and follow-up, with children sitting on a school chair, using headlamps, plane mouth mirrors and a periodontal probe. Teeth will not be brushed or professionally cleaned before examination but cotton wool rolls/buds and the periodontal probe will be used, respectively, to dry the surfaces and remove moisture/debris to facilitate visual inspection. Standard infection control measures will be in place.

After clinical examinations at baseline and follow-up, 10% of participants will be re-examined by the same fieldwork team to assess intra-examiner reliability. After clinical examinations in the follow-up assessment (at 12 months) screened-positive children in both trial groups will be referred to KSU-DC (close-out procedure).

Given the training and calibration of examiners in caries assessment, the probability of having false-positive cases is minimal. Upon referral, a standard dental check-up is always conducted as part of the treatment plan where any false-positive cases will be identified. If that occurs, the dentist will inform parents that upon further examination no treatment is required.

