### Trial design

This will be a cluster randomised, assessor-blinded, superiority trial with two groups running in parallel and an allocation ratio of 1:1. The trial will be conducted over 12 months, from baseline to follow-up outcome assessments. Randomisation at cluster level (school) will prevent contamination that could arise from delivering both interventions in the same school (i.e. randomisation at child level) while also accounting for variations between schools and areas in which the schools are located.

The trial is sponsored by King’s College London. It is a PhD project carried out by the principal investigator (HA) and supervised by WS and EB. The progress of the study will be closely monitored by a PhD Committee (acting as a Trial Steering Committee), including the principal investigator, the two supervisors and two independent external examiners.

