#### Secondary outcomes

The change in the proportion of children having teeth with untreated caries and the change in the proportion of children who reported visiting a dentist (as reported by parents and children) during the duration of the trial will be the secondary outcomes.

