#### Ensuring participant retention

Given that this is a 12-month trial, baseline and follow-up data will be collected in separate school years (summer holidays in-between). This implies that there might be some losses to follow-up as children might change residence/school. We have increased the trial size accordingly to compensate for 11% attrition (i.e. derived from the proportion of children continuing in the same school the following year). Fieldwork teams will stay in schools for an entire week (as they progress screening children from one classroom to another) to give an option to those children who were absent the day that their classroom was screened. That aside, we expect a high completion rate as parental consent will be sought for both waves of data collection simultaneously. Using a clinical outcome measure will prevent further losses to follow-up as schools are captive populations. Attrition could be higher for parental questionnaires (used to estimate child dental visits). However, we are also collecting information on dental visits from the children’s perspective. Furthermore, dental visits are the secondary outcome and will not affect the main conclusion of the trial.

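### At follow-up the parent item looks back 12 months while the child item looks back to baseline; only the child item matches the outcome definition (minor)

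*Protocol article*

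**What the plan says.** The second of the two secondary outcomes (Secondary outcomes) is "the change in the proportion of children who reported visiting a dentist (as reported by parents and children) during the duration of the trial". It has two informants and one stated period, the trial itself.

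Data collection describes the two follow-up instruments.

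- **Parents:** a short form "focussing on the child’s last dental visit during the last 12 months", which "will be sent to all parents a week prior to the second visit to schools for the follow-up clinical examinations".
- **Children:** at baseline, "the recorder will ask children whether they had visited the dentist in the last 12 months". At the second visit the anchor changes: "The same question will be asked to children during follow-up clinical assessments (‘since we last saw you".

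The planned spacing is under Trial design: "The trial will be conducted over 12 months, from baseline to follow-up outcome assessments". The article gives no tolerance around it. Ensuring participant retention adds that "baseline and follow-up data will be collected in separate school years (summer holidays in-between", and that teams remain in each school for a week so that absent children can be examined on another day.

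**The concern.** The child item was re-anchored to the baseline examination for follow-up. The parent item was left on a rolling 12-month recall counted back from the day the form is filled in. The two informants therefore report on different periods for the same outcome, and only the child's period is the one the outcome names.

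A rolling window matches the trial period only if the form is completed exactly 12 months after baseline. Completed earlier, it admits visits made before the child was screened, which referral cannot have caused. Completed later, it cuts off the days just after the referral letter. Either error adds misclassification to the comparison of attendance.

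Attendance is a secondary outcome, but it has a job in this trial. Promoting it is part of the primary aim, and the Discussion reads it alongside caries to judge whether a null result points to the services or to the screening process as a whole.

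**Working it through.** The plan gives no figure on this point to reproduce, so the check is date arithmetic.

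**Inputs**

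- Day 0 is the child's baseline examination; F is the day of the follow-up examination.
- Planned F = 365 (12 months, Trial design). Every other F below is an assumption.
- Parent recall is 365 days back from completion (Data collection).
- The form is completed L days before the follow-up examination, with L between 7 (the day it is sent) and 0 (the day of the visit).
- The child's window is day 0 to day F.

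**Formulas**

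- Parent window: from F − L − 365 to F − L.
- Days before baseline wrongly included = max(0, −(F − L − 365)).
- Days after baseline missed at the start = max(0, F − L − 365).
- Days missed at the end = L, so 0 to 7 whatever F is.

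**Planned interval, F = 365**

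- L = 7: start 365 − 7 − 365 = −7, end 358. Seven days before baseline are included and the last 7 are missed.
- L = 0: start 365 − 0 − 365 = 0, end 365. The window coincides with the child's.
- For any L from 0 to 7, no day after referral is missed at the start.

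**Other intervals (assumed)**

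| F | Parent window starts, L = 7 to L = 0 | Pre-baseline days included | Early post-baseline days missed |
|---|---|---|---|
| 335 (about 11 months) | −37 to −30 | 30–37 | 0 |
| 365 (planned) | −7 to 0 | 0–7 | 0 |
| 372 (one week late) | 0 to 7 | 0 | 0–7 |
| 379 (two weeks late) | 7 to 14 | 0 | 7–14 |
| 395 (about 13 months) | 23 to 30 | 0 | 23–30 |
| 425 (about 14 months) | 53 to 60 | 0 | 53–60 |

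**Who is misclassified.** A child is a false negative on the parent form only if every visit since baseline falls in the missed days. A child is a false positive only if there was a visit in the extra pre-baseline days and none since baseline. A child who attended early and again later is still counted correctly.

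**With a baseline anchor.** The parent window becomes day 0 to F − L for any F. Nothing is lost or added at the start; the 0 to 7 days at the end remain, because the form goes out before the visit.

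**The case against.** The strongest reply is that the schedule already protects the outcome. At the stated 12 months the parent window opens at or just before baseline, so the weeks after referral are covered. That stands, and it limits the point to about a week at each end under the plan.

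A reader might infer more: that the parent form will lose the weeks just after referral and so bias the attendance effect towards zero. The document does not support this.

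- Recruitment from November 2017 to April 2018 shows staggered entry, not unequal intervals; each school can be revisited a year after its own baseline.
- Separate school years are what any 12-month interval across a summer holiday produces.
- Nothing says that referral visits cluster early, or that intervals will differ between groups.
- Ensuring participant retention says that children's reports are also collected. It states no rule that they replace missing parent forms, so it does not follow that the period measured depends on who answered.

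Two further replies carry some weight. First, the article summarises a questionnaire that is not shown, and the actual item may already name the baseline visit. If so, only the description needs aligning. Second, the outcome is a change in proportion, and a 12-month recall at both waves keeps the periods equal in length. That is a real advantage. It does not outweigh the mismatch, because the outcome is defined over the trial period and the child item has already been moved to that anchor.

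Parents will also not apply 12 months to the day, and a child's examination day can shift within the school week, so the day counts are approximate.

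**Conclusion.** The mismatch of anchors is on the page and needs no assumption: two sources for one outcome, two recall periods, and only the child's agrees with the definition. Its consequence under the planned schedule is small, at most about 7 pre-baseline days counted and about the last 7 days missed. Larger errors, in either direction, depend on intervals of 11, 13 or 14 months that are assumed here for illustration and appear nowhere in the document. The effect is confined to the parent-reported part of one secondary outcome and to children whose sole visit falls in the affected days. The clinical primary outcome is unaffected. Minor, but worth correcting because the correction is so cheap.

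**What to change.** Reword the parent follow-up item to ask about the period *since the school dental examination in [month/year of that school's baseline visit]*, in line with the child item and the outcome definition. Record the actual interval between the two examinations for each child. No rule ranking parent over child reports is needed for this, and there is no need to ask about visits other than the last: if the last visit was before baseline, there was none during the trial.

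The cost is one questionnaire item and a minor ethics notification. There was time for it: recruitment opened on 20 November 2017, so no 12-month follow-up falls due before 20 November 2018, after the 13 March 2018 date of protocol version 3. The downside is that the follow-up item no longer mirrors the baseline 12-month wording and its period varies with the interval, which is why the interval should be recorded.

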### Trial outcome

Combining clinical and self-reported outcomes will provide more robust evidence on the effectiveness of school-based dental screening. While self-reported dental visits are a direct indicator of the impact of the intervention, they are a surrogate measure of clinical status and subject to measurement bias. We have, therefore, chosen a clinical measure as primary outcome as it will confirm that a dental visit occurred during the trial period. A clinical measure also allows a blinded outcome assessment (caries examination), something that could not be achieved with self-reported dental visits as participants will know which group they are in.

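### The visit question, put to each child by one of the examining pair, can cue the examiner before caries is scored at follow-up

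*Protocol article*

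**What the plan says.** The protocol's Data collection section sets out the order of events at the school visit: "Before examining every child, the recorder will ask children whether they had visited the dentist in the last 12 months". Where a child reports a visit, the recorder also notes why it took place. For the second wave the section adds: "The same question will be asked to children during follow-up clinical assessments", worded to cover the time since the baseline visit.

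The same section describes the team: "Each fieldwork team will consist of an examiner who will perform clinical examinations and a recorder who will register codes in examination forms". It continues: "Individuals will switch roles to minimise visual fatigue". On the two waves it says: "Examinations will be conducted similarly at baseline and follow-up".

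The Trial design section calls the trial assessor-blinded. The Trial outcome section gives blinding as a reason for a clinical primary outcome: "A clinical measure also allows a blinded outcome assessment (caries examination". It contrasts this with self-reported visits, where participants know their group. The Blinding section gives the mechanism: "Outcome assessors will be blinded by sending separate fieldwork teams (who will not be aware of the study aims) for the intervention and comparison groups".

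**The concern.** At baseline the order does no harm, because no child has yet been referred. At follow-up the child may have been referred and treated in between, and the examiner is about to score the primary outcome. The answer to the visit question is the self-report that the protocol declined to use as primary outcome because it is open to influence from knowledge of the group. As written, that self-report is given to one of the two people doing the examination, just when it can affect the score.

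At stake is differential measurement error. Judging whether a tooth has untreated decay involves doubtful cases. If examiners resolve these differently for children they have just heard were treated, and such children are more common in one arm, part of the between-group difference comes from the scoring and not from the treatment. Because the baseline score is unaffected, any such error passes in full into the change from baseline.

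**Working it through.** The protocol states no figure on this point, so there is none to reproduce. The check sets the sections side by side and then asks how much a reply can tell the examiner.

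**1. Order at follow-up.** Asking before examining is stated for the first visit. For follow-up the text says only that the same question is put during the assessments. That it is the same question, and that examinations run alike at both waves, makes the same order the natural reading, but it is an inference. The same holds for recording the reason. No sentence moves the question to after charting.

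**2. Who hears the answer.** Recorder and examiner form one team and exchange roles, so the person who asks is an examiner at other times. No sentence separates the question from the examination or puts it out of the examiner's hearing.

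**3. What the answer can reveal.** The question covers whether a visit took place and why. It does not ask about arm, letter or facility. Under Trial interventions, screened-positive children in both arms take home a referral letter and screened-negative children in both arms get none, so visits and non-visits occur in both. Intervention referrals, however, name one facility, and under Blinding families learn their group from the letter. A child who volunteers the facility's name could give the arm away.

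**4. How strong a clue a visit is.** Let p_I and p_C be the shares of children reporting a visit in the intervention and comparison arms. With 1:1 allocation:

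- P(intervention | visit) = p_I / (p_I + p_C)
- chance of guessing the arm correctly from one child's yes or no = 0.5 + |p_I − p_C| / 2

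The protocol gives no attendance rates, so those below are assumptions. For 50% against 30%: 0.50 / 0.80 = 0.625, and 0.5 + 0.20 / 2 = 0.60.

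| Assumed attendance, intervention / comparison | P(intervention given a visit) | Correct guess of arm |
|---|---|---|
| 30% / 30% | 0.50 | 50% |
| 40% / 30% | 0.57 | 55% |
| 50% / 30% | 0.625 | 60% |
| 60% / 30% | 0.67 | 65% |
| 80% / 20% | 0.80 | 80% |

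Visit status alone is a partial clue to the arm.

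**5. Bias without knowledge of the arm.** Let d be the mean number of teeth per attending child that the examiner scores as not decayed only because of having heard of the visit. If d is the same in both arms, the bias in the group difference is (p_I − p_C) × d. The Primary outcome section assumes that the intervention works through dental visits, so the protocol itself expects p_I to exceed p_C. The bias then favours the intervention whenever d is above zero. Inter-examiner kappa for caries at tooth level is 0.78, so some calls are doubtful and d need not be zero. Neither d nor the attendance rates are in the document.

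**6. Carry-over.** Arms are whole schools, and the retention section keeps teams in a school for a full week. One reply that reveals the arm can therefore inform later examinations in that school.

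**The case against.** The strongest reply is that the protocol has a safeguard: teams do not know the study aims, and referral letters are handed out by people other than the examining pair. A team without a hypothesis has none to favour. This stands against the idea that examiners would knowingly score towards a wished-for result. It does not answer the attendance cue. Expecting fewer decayed teeth in a child who has just reported treatment takes no knowledge of the aims.

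A second reply is that the follow-up order is inferred. That is true, and the text should settle it.

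A third is that fillings and extractions are visible in the mouth, so the examiner will often know that a child was treated whatever the order. This also stands. The question adds to a cue that is partly there already, and changing the order removes only the added part.

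A reader might go further and infer that the question unblinds the examiner to the arm, or that the assessor-blinded description is therefore false. The document does not support that. Visits and letters occur in both arms and the facility is not asked for. Even a reply naming the university college is not conclusive, because the Background lists university hospitals among the existing free services and nothing stops comparison families from using them.

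**Conclusion.** The point holds as a weakness in procedure. A member of the examining pair obtains information on attendance at the follow-up session, probably before caries is scored, with no stated barrier to the examiner. This can reveal attendance, and in some children the arm, and so opens a route to differential error in the primary outcome that the stated safeguard does not close.

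The conclusion rests on three things: that the order at follow-up matches baseline; that attendance differs by arm, as the protocol expects; and that hearing of treatment can sway a doubtful call. If attendance were equal in the two arms, the attendance cue alone would cause no average bias between groups.

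The size cannot be estimated from the document. A reader might try to turn the kappa of 0.78 into a number of teeth and compare it with the 0.50-tooth target difference. That would need an assumed tooth count, caries prevalence and share of calls swayed, and the result would also depend on whether calls shift in one arm or in both. None of this is given. The case for acting is that the remedy is nearly free.

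**What to change.** State the order for the follow-up visit: complete and lock the child's caries chart, then ask the visit question. Since one child's reply can affect later examinations, it is better to ask after the whole class has been examined, or to have the question put by someone outside the examining pair who is unaware of allocation and out of the examiner's hearing. Ask children not to talk about dental visits during the examination. Recording the examiner's guess of the arm at the end of each school would show how well blinding held.

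The principal investigator should not take over the question. That role is told the allocation (Randomisation section) and hands out the letters in girls' schools (Data collection section), so an unblinded person would then be collecting a self-reported secondary outcome.

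Re-ordering costs a change to the fieldwork form and a line in the team briefing; a separate interviewer would cost some staff time. Recruitment began on 20 November 2017 and follow-up comes 12 months after baseline, so at protocol version 3 (13 March 2018) the follow-up visits were still ahead. The baseline order need not change. Visible dental work will still show that some children were treated, and the report should say so.
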